**Secondary Outcomes**

- Changes in weight from baseline to 6 weeks, and to 3 months and 6 months.
- Changes in blood pressure from baseline to 3 months and 6 months,
- Changes in lipid profile from baseline to 3 months;
- Participant feedback and ratings of the intervention, including the helpfulness of the intervention, recommending it to friends, readiness to continue, barriers and facilitators, and most popular 8-hour time frames.
- Changes in ratings of the difficulty adhering to TRE and ratings of hunger over time
- Estimates of effect size for future randomised trials, if TRE is deemed feasible and efficacy is encouraging.
- Comparison of weight changes in TRE to weight changes in other weight-loss cohorts in our previous trials and community clinics.

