**Subject withdrawal**

Participants will be able to stop the TRE intervention at any time. Participants who stop the intervention will be followed up at 6 weeks and 3 months, unless they do not wish to be.

Unless withdrawn participants request otherwise, data collected up to the point of their withdrawal will be used in the study analysis. Withdrawn participants will not be replaced.

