# STATISTICAL CONSIDERATIONS

**Sample Size**

In this early phase exploratory research, we opted for a pragmatic sample size of 50, achievable economically and quickly, but large enough to provide reasonable confidence intervals on key estimates.

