**Statistical Analysis**

Descriptive statistics will be used to report on proportions of participants adhering to TRE; the 8-hour time frames most commonly selected; and client feedback ratings. Paired samples t-test will be used to examine any significant changes from baseline to follow-up in weight, BMI, blood pressure, and blood lipid profiles.

Adherence rates to TRE and weight/BMI changes will be compared against previous weight-loss intervention cohorts (e.g. our previous trials, community weight clinic), via Chi-square analysis for categorical variables and ANOVA for continuous variables.

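### The cohort comparison of weight and BMI change names ANOVA without an unequal-variance form; if cohorts differ from TRE in both size and spread, its error rate and standard error are off

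*Protocol*

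**What the plan says.** The Statistical Analysis section of the protocol states that "weight/BMI changes will be compared against previous weight-loss intervention cohorts", with the tests given as "via Chi-square analysis for categorical variables and ANOVA for continuous variables". The statistical row of the Synopsis repeats this. Neither place says whether variances are pooled.

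The comparison serves the second aim in the Synopsis, weight loss relative to other methods, and is the last item under Secondary Outcomes: "Comparison of weight changes in TRE to weight changes in other weight-loss cohorts in our previous trials and community clinics". The number of cohorts, their sizes and their SDs are not given, and no significance level is stated.

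On the TRE side, Sample Size says "we opted for a pragmatic sample size of 50", justified as "large enough to provide reasonable confidence intervals on key estimates". Under Subject withdrawal, "Withdrawn participants will not be replaced". Change within the TRE group is handled separately, by paired t-tests.

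**The concern.** The classical ANOVA F test estimates one common variance from all groups. In a randomised trial with equal arms that assumption is fairly harmless. Here the groups are one cohort of at most 50 and an unspecified set of other interventions from other trials and clinics. Nothing in the design holds their sizes or their spread of weight change equal to those of TRE.

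When sizes differ, the pooled variance is weighted towards the larger group. When SDs differ as well, the standard error of the TRE-minus-cohort difference is wrong:

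- If the smaller TRE group is the more variable, the standard error is too small and differences are declared too often.
- If TRE is the less variable, the standard error is too large and real differences are missed.

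The result at stake is the comparison with other methods, which would naturally be read alongside the fourth aim, whether a larger controlled trial is worthwhile.

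**Working it through.** **The plan's own figure.** The sample size of 50 comes with no alpha, power, SD or effect size, so there is nothing to reproduce.

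**Inputs.**
- From the protocol: TRE n₁ = 50, falling with withdrawals.
- Assumed, because the protocol does not give them: one comparator of n₂ = 50, 100, 200 or 500; TRE/cohort SD ratio r from 0.5 to 2, with cohort SD = 1; two-sided 5%; 40 TRE completers as a sensitivity value.

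**Formulas (two groups, no true difference).**
- Pooled variance: s² = [(n₁−1)r² + (n₂−1)] / (n₁+n₂−2)
- Pooled SE: √[s²(1/n₁ + 1/n₂)]
- True SE: √(r²/n₁ + 1/n₂)
- Approximate type I error: 2 × [1 − Φ(t × pooled SE / true SE)], where t is the two-sided 5% critical value on n₁+n₂−2 degrees of freedom

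**Worked case, 50 vs 200, r = 1.5.**
- s² = (49×2.25 + 199)/248 = 1.247
- Pooled SE = √(1.247×0.025) = 0.177
- True SE = √(0.045 + 0.005) = 0.224, so the SE ratio is 0.79
- The critical value 1.970 becomes 1.970×0.79 = 1.56 true SEs: type I error about 12.0%

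**Worked case, 50 vs 200, r = 0.67.**
- s² = (49×0.4489 + 199)/248 = 0.891
- Pooled SE = 0.149; true SE = √(0.00898 + 0.005) = 0.118; ratio 1.26
- Effective critical value 1.970×1.262 = 2.49: type I error about 1.3%

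**Simulation** (40,000 normal data sets per setting), type I error of the pooled test with TRE n = 50:

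| Cohort n | r = 0.5 | 0.67 | 0.8 | 1 | 1.25 | 1.5 | 2 |
|---|---|---|---|---|---|---|---|
| 50 | 0.051 | 0.051 | 0.051 | 0.049 | 0.049 | 0.048 | 0.050 |
| 100 | 0.018 | 0.025 | 0.035 | 0.052 | 0.069 | 0.085 | 0.107 |
| 200 | 0.004 | 0.013 | 0.026 | 0.051 | 0.087 | 0.122 | 0.182 |
| 500 | 0.001 | 0.007 | 0.019 | 0.050 | 0.101 | 0.159 | 0.253 |

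The 50-vs-50 row and the r = 1 column are nominal: both conditions are needed. The hand calculations match the simulated 0.122 and 0.013.

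With 40 TRE completers and a cohort of 200, the pooled test gives 0.012, 0.133 and 0.201 at r = 0.67, 1.5 and 2. An omnibus F test on three groups of 50/200/200 gives 0.028, 0.113 and 0.178 at the same ratios.

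**Same settings with Welch's test.** Across all the two-group settings, with 50 or 40 TRE participants, the type I error is 0.047 to 0.053.

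**Cost when variances are equal.** For a true difference of 2.8 standard errors (pooled power about 80%), 400,000 simulations gave pooled versus Welch power of 79.5% vs 79.2% (50 vs 100), 79.6% vs 78.9% (50 vs 200), 79.7% vs 78.8% (50 vs 300) and 79.7% vs 78.6% (40 vs 200). The loss is at most about 1 point.

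**The case against.** **The protocol never says pooled.** ANOVA can be read as a family of methods, and the variance form is often settled in an analysis plan, which is not shown here. This stands in part: the wording does not rule out Welch. But the test is named in two places, the unqualified name ordinarily denotes the pooled F test, and an analyst following the text would run that.

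**Both conditions for harm are assumed.** This stands. No cohort size or SD is in the protocol. A reader might infer that the comparators are larger and more or less variable than TRE, and hence that the comparison certainly carries wrong error bars. The protocol does not support that: with equal sizes or equal SDs the pooled test is nominal, and with moderate imbalance the error is mild.

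**The reach is narrow.** This also stands. A reader might infer that the uncertainty of the TRE weight result itself is borrowed from other people's data. It is not: change within TRE is assessed by paired t-tests, which use TRE participants only. The primary outcome is adherence, the weight comparison is one of several secondary outcomes in a study that calls itself exploratory, and no alpha or decision threshold is attached to it.

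**Confounding may matter more.** Differences in population and conduct between non-randomised cohorts would affect this comparison under any variance estimator. That is true, and Welch does not help with it. It is no reason to keep a standard error that may also be miscalibrated when the alternative costs almost nothing.

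**Conclusion.** The point holds as a conditional and limited one. The protocol names a test whose usual form assumes equal variances, for groups that nothing in the design makes alike in size or spread. If cohorts differ from TRE in both respects, the comparison can be too liberal or too conservative. Under the assumptions above, a two-sided nominal 5% becomes about 1.3% to 12% for 50 versus 200 at SD ratios 0.67 to 1.5, and about 3.5% to 7% for 50 versus 100 at ratios 0.8 to 1.25. The direction cannot be predicted from the protocol.

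The figures rest on assumed cohort sizes and SD ratios, normal data and the pooled form of ANOVA. They show what could happen and do not estimate what will. No primary conclusion depends on this test.

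**What to change.** In the statistical row of the Synopsis and in Statistical Analysis, replace ANOVA with Welch's (unequal-variance) ANOVA, and report a Welch confidence interval for each TRE-minus-cohort difference in weight and BMI change. If a regression model is used instead, specify heteroscedasticity-robust standard errors.

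The change is one line of wording and a software option. It should be accompanied by a plain statement that the comparison is non-randomised, so that calibrated intervals are not mistaken for protection against cohort differences.

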# ETHICS

The study will be carried out in accordance with the ethical principles in the Research Governance Framework for Health and Social Care, Second Edition, 2005 and its subsequent amendments as applicable and applicable legal and regulatory requirements.

This protocol and any subsequent amendments, along with any accompanying material provided to the participants and any advertising material will be submitted by the Chief Investigator to the sponsor and REC.

The CI will send the Annual Progress Report to the main REC and to the QMUL JRMO using the NRES template.

Participant identifiable data will remain confidential, and will be handled, processed, stored and destroyed according to the terms of the Data Protection Act 1998. All study data collected will be stored securely, and anonymised, and will not contain any identifying information. Only study staff and representatives of the sponsor or regulatory authorities (to the extent that they are allowed by law) will have potential access to view study data.

**Conflicts of Interest**

No applicant declares any conflict of interest.

# DATA HANDLING AND RECORD KEEPING

**Confidentiality**

Only study personnel and the study sponsor will have access to study data. We will not request any information about participants from their doctors.

Participants will not be identifiable from their study data. They will be assigned a participant ID number. Study data will be collected on paper CRFs, and will contain the participant ID only. Patient identifiable data will be entered onto a spreadsheet, for the purposes of contacting participants throughout the study. This data will be kept securely, and separately to the CRFs. The spreadsheet will be password protected and held on an encrypted USB stick. When not in use, the USB will be stored in a locked drawer. Original paper copies will be filed and kept in a locked cabinet. Only study staff will have access to the USB and paper copies.

All information will be kept confidential. Copies of all documents regarding the study will be kept in the trial master file (TMF) and/or relevant site file.

**Record Retention and Archiving**

All paper information relevant to the study will be archived and retained for 20 years at the Barts Health NHS Trust facility in [name]. The sponsor will be informed in writing when and where all data is archived.

# LABORATORIES

**Central Laboratories**

Lipid profile analysis will be conducted by the Doctors Laboratory Ltd. ([name]).

## Sample Collection, Labelling and Logging

Samples would be collected by trained phlebotomists in accordance with the Doctors Laboratory instructions, and labelled with participant ID number, time-point/session number, and date.

All samples taken will be logged.

**Sample Storage Procedure**

Samples will be temporarily stored at the Health and Lifestyle Research Unit (for up to 2 days maximum), at ambient room temperature, in a secure cabinet which only study staff will have access to.

## Sample Receipt

Samples will be sent to the central lab via their courier service. Upon receipt of the samples, the laboratory would ensure that the physical integrity of these samples have not been compromised in transit. If they have, the CI and sponsor will be informed of this. Upon receipt of samples, laboratory staff would also ensure that all samples are accounted for.

## Sample Analysis

A full Lipid profile will be obtained, including Total Cholesterol, Triglycerides and HDL Cholesterol. Total Cholesterol and Triglycerides will be analysed using the enzymatic, colorimetric method; and HDL Cholesterol with the homogeneous enzymatic colorimetric test.

**Sample destruction**

When all the samples have been analysed and the data has been entered, the samples will be destroyed by the Doctors Laboratory in accordance with the Human Tissue Authority’s Code of Practice.

# MONITORING & AUDITING

Monitoring will be proportional to the objective, scope, design, size, complexity and risks of the project. QMUL JRMO will risk assess the trial in line with the QMUL JRMO risk assessment SOP. The trial’s risk assessment will be used by the Study Manager and CI/PI to create a monitoring plan (detailing the type, duration and frequency of monitoring). A Copy of the plan will be kept in the TMF. The CI will ensure that the agreement/wording is not altered without written authorisation (email confirmation) from the QMUL JRMO; all new versions will be signed.

CI/study team will notify the QMUL JRMO’s GCP team once the first patient has been consented. .

# TRIAL COMMITTEES

A Trial Management Group (TMG), consisting of the CI, study manager and other key study staff, will meet every month during the recruitment phase, to oversee the running of the project**.**

# FINANCE AND FUNDING

The Study is funded by a Project Grant from British Heart Foundation (£61,574).

# INDEMNITY

The study Sponsor in the UK will be QMUL.QMUL JRMO has arranged for suitable indemnity concerning negligent harm to be in place for the study in the UK.

The insurance that QMUL has in place provides "No Fault Compensation" for participants which provides an indemnity to participants for non-negligent harm.

# DISSEMINATION OF RESEARCH FINDINGS

Study results would be:

(1) Communicated to the BHF

(2) Published in Open Access format in a prominent journal.

(3) Presented at a conference on obesity

